## Abstract

**Background:**

While eating disorder not otherwise specified (EDNOS) is the most common eating disorder (ED) diagnosis in routine clinical practice, no specific treatment methods for this diagnosis have yet been developed and studied. Enhanced cognitive behavioral therapy (CBT-E) has been described and put to the test as a transdiagnostic treatment protocol for all EDs, including EDNOS. Initial research in the UK suggests that CBT-E is more effective for EDs, especially bulimia nervosa (BN) and EDNOS, than the earlier version of CBT. These positive results of CBT-E have to be replicated in more detail, preferably by independent researchers in different countries. Being the first Dutch study into CBT-E, the results from this national multicenter study – on three sites specialized in EDs – will deliver important information about the effectiveness of CBT-E in several domains of ED pathology, while providing input for the upcoming update of the Dutch Multidisciplinary Guideline for the Treatment of Eating Disorders.

**Methods/design:**

A multicenter randomized controlled trial will be conducted. One hundred and thirty-two adult outpatients (aged 18 years and older) with an ED diagnosis and a Body Mass index (BMI) of between 17.5 and 40 will be randomly allocated to the control or the intervention group. Subjects in the control group will receive Treatment as Usual (standard outpatient treatment provided at the participating sites). Subjects in the intervention group will receive 20 sessions of CBT-E in 20 weeks. The design is a 2 (group) × 5 (time) repeated measures factorial design in which neither therapists nor patients will be blinded for treatment allocation. The primary outcome measure is recovery from the ED. Secondary outcome measures include ED psychopathology, common mental disorders, anxiety and depressive symptoms, health-related quality of life, health care use and productivity loss. Self-esteem, perfectionism and interpersonal problems will be examined as putative predictors and mediators of the effect of treatment. Also, an economic evaluation from a societal perspective will be undertaken. All relevant effects, direct and indirect costs will be included. Utility scores will measure the effects. Measurements will take place at pretreatment, 6 weeks, 20 weeks, 40 weeks and 80 weeks.

**Discussion:**

This effectiveness study into CBT-E has the aim of broadening the scope and generalizability of former studies. If CBT-E appears to be at least as effective as traditional diagnosis-specific treatments for a broad range of ED patients, training in one protocol would be sufficient for clinicians to treat patients with different kinds of EDs. It gives the opportunity to offer treatment for a severe mental disorder with fewer resources, thereby increasing the accessibility of specialized care for patients with an ED.

**Trial registration:**

Netherlands Trial Register, NTR4485. Registered on 2 April 2014.

**Electronic supplementary material:**

The online version of this article (doi:10.1186/s13063-016-1716-3) contains supplementary material, which is available to authorized users.

## Background

Eating disorders (EDs) are severe mental disorders, which typically begin in adolescence [1–4]. In the fourth edition of the *Diagnostic and Statistical Manual of Mental Disorders* (DSM-IV) [5] three EDs are recognized: anorexia nervosa (AN), bulimia nervosa (BN) and a residual diagnostic category called eating disorder not otherwise specified (EDNOS) including binge eating disorder (BED). In the new edition, DSM-5 [6], BED has been added as a new official diagnosis [7]. Prior to the official recognition of BED as a specific DSM-5 ED, several studies into the efficacy of specific BED interventions have been performed [8], utilizing DSM-IV research criteria. In DSM-5, the remaining EDs from the DSM-IV EDNOS category have been redefined into two categories: other specified feeding or eating disorder (OSFED) and unspecified feeding or eating disorder (USFED).

These developments have complicated direct comparisons between research data on the DSM-IV EDNOS and the DSM-5 BED, OSFED and USFED categories.

The effectiveness research on EDs has focused on BN and, more recently, BED. Studies of good quality on DSM-IV EDNOS (with the exception of BED) and AN are limited. This paucity of research on ED symptoms summarized in the DSM-IV EDNOS category is a serious problem, as EDNOS has been the most common ED diagnosis (50–77%) in routine clinical practice [9, 10], and is responsible for severe morbidity, loss of quality of life and even an annual mortality rate of 3.3 per 1000 person years [11]. General health care utilization among this group of patients is high [12], and about 62% are referred to mental health care by their GPs [13].

EDNOS often refers to ED psychopathology that does not meet the full diagnostic criteria of one of the specific EDs (i.e., AN or BN). Examples are: (in women) all symptoms of AN except amenorrhea, and compensatory behavior by individuals of normal weight after eating small amounts of food. Although the use of DSM-5 criteria effectively reduces the frequency of the residual diagnosis EDNOS (for example, by lowering the threshold for AN and BN and adding BED as a specified ED), the magnitude of this reduction varies across studies [14].

The three most prominent guidelines – from the UK National Institute for Health and Care Excellence in 2004 [15], from the American Psychiatric Association in 2006 [16] and the most recent from the Royal Australian and New Zealand College of Psychiatrists in 2014 [17] – recommend cognitive behavioral therapy (CBT) as the psychological treatment of first choice, specifically for BN and BED. Specific treatment recommendations for AN are less forthcoming due to the paucity of positive outcome data in this area. These recommendations concur with those from the Dutch Multidisciplinary Guideline for the Treatment of Eating Disorders in 2006 [18].

[name] [19] developed a relatively short transdiagnostic CBT, CBT-E(nhanced), designed to be suitable for the full range of ED diagnoses. CBT-E is based upon the transdiagnostic theory of the maintenance of EDs, in which it is assumed that most of the mechanisms involved in the persistence of EDs are common to all three EDs, rather than being specific to each diagnostic group separately [20]. According to [name] and colleagues, EDs have more similarities than differences, especially the core psychopathology (over-evaluation of shape and weight) and expression in attitudes and behavior (dietary restriction, dietary rules, binges, self-induced vomiting, etc.). CBT-E, the enhanced version of CBT, uses new strategies and procedures to address mechanisms that are central to the maintenance of all EDs, including the diversity of ED psychopathology that until recently comprised the DSM-IV EDNOS category. CBT-E is characterized by increased focus on engagement, greater emphasis on the modification of concerns about shape and weight, and the development of skills to deal with setbacks. Regardless of ED diagnosis, CBT-E is designed as an individualized and “modular” form of treatment, in which specific modules may be directed at the particular maintaining mechanisms operating in the individual patient’s case.

There are two forms of CBT-E: a focused form (CBT-Ef) that targets ED psychopathology exclusively (e.g., procedures directed at over-evaluation of shape and weight), and a more complex broad form (CBT-Eb) that also addresses additional problems that appear to maintain EDs or complicate their treatment. [name] et al. [21] state that additional mechanisms such as clinical perfectionism, low self-esteem and interpersonal problems maintain the ED psychopathology and thereby obstruct change during the treatment with CBT-E. The broad version of CBT-E was designed to focus on these mechanisms. For both versions of CBT-E two variants of intensity have been developed: 20 sessions in 20 weeks for the patients who are not significantly underweight (Body Mass Index (BMI) above 17.5), and 40 sessions in 40 weeks for the patients who are significantly underweight (BMI below 17.5).

First studies have found CBT-E to be more efficacious than other psychological approaches [22–24]. It seems feasible to treat a broad range of ED patients with CBT-E, but more evidence is required according to a recent meta-analysis [25] and the most recent guidelines [17]. The current study will not only evaluate the effectiveness of CBT-E in terms of the reduction of ED psychopathology and additional comorbid psychopathology and enhancement of quality of life and health status, but also the cost-effectiveness of CBT-E relative to regular ED therapy. Treatment as Usual (TAU) for patients with an ED varies per ED category. For BN and BED there are well-described and evaluated CBT protocols [26, 27]. For AN and EDNOS (except BED) evidence-based treatment protocols are lacking and treatments vary greatly. There are no empirical data about duration, intensity and costs of regular therapy for EDs in The Netherlands. However, consulted independent ED experts in the Netherlands and Belgium have estimated that TAU for EDs is probably more intensive, long-term and less effective than CBT-E. Therefore, we expect CBT-E to be more cost-effective compared to regular treatment.

If CBT-E indeed appears to be at least as effective as traditional diagnosis-specific treatments for a broad range of ED patients, this unified transdiagnostic approach for all EDs would give the opportunity to offer treatment for a severe mental disorder with fewer resources and, therefore, increase the accessibility of an evidence-based treatment for patients with an ED.

In this study we only use the focused version (CBT-Ef) for patients with a BMI above 17.5. BMI above 17.5 is considered by [name] as the critical limit for the 20-session CBT-E variant. Additional measurements on top of the outcome measures and those for quality of life and health status involve perfectionism, self-esteem and interpersonal problems. These are believed to be possible clinical and research indications for obstruction in change and progress. Measurements will be taken before, during and after treatment to explore the predictive and mediating effects on treatment outcome.

## Methods/design

### Design

We will execute a multicenter randomized controlled trial (RCT) with two equal-sized parallel groups at three specialized ED treatment centers from three regions in The Netherlands. Participants will be randomized into two groups (CBT-E versus TAU) stratified by ED center and type of ED. Measurements will take place at pretreatment, 6 weeks, 20 weeks, 40 weeks and 80 weeks, resulting in a 2 (group) × 5 (time) repeated measures factorial design. For an overview of the proposed flow of participants, see Fig. 1. The present study protocol was written in accordance with the Standard Protocol Items: Recommendations for Interventional Trials (SPIRIT) [28]; copies of the SPIRIT Checklist and figure have been included in Additional files 1 and 2.

**Fig. 1 Fig1:**
[figure not shown]
Proposed flow of participants. *T0* baseline, *T1* week 6, *T2* end of treatment week 20, *T3* follow-up week 40, *T4* follow-up week 80. *SCID-I* Structured Clinical Interview for DSM Axis-I disorders, *EDE-Q* The Eating Disorder Examination-Questionnaire, *WSQ* Web Screening Questionnaire for common mental disorders, *MASQ* Mood and Anxiety Questionnaire, *EQ-5D* EuroQoL five dimensions questionnaire, *SF-36* Short Form Health Survey, *TiC-P* Trimbos/iMTA Questionnaire for Costs associated with Psychiatric Illness, *RSE* Rosenberg Self-Esteem Scale, *IAT* Implicit Association Test Self-Esteem. *F-MPS* Frost Multidimensional Perfectionism Scale, *IIP-32* Inventory of Interpersonal Problems

### Participants

Participants will consist of 132 adult outpatients aged from 18 years with an ED diagnosis according to DSM-5 and a BMI of between 17.5 and 40. They are recruited at the participating mental health centers: PsyQ/Parnassia Psychiatric Institute in The Hague will include 60 patients and PsyQ/Lentis Psychiatric Institute in Groningen and Rintveld/Altrecht Mental Health Institute in Zeist both 36 patients.

### Inclusion criteria

In order to be eligible to participate in this study, a participant must meet all of the following criteria:Adult outpatients (from age 18 years) with an ED diagnosis: AN, BN, BED, OSFED (EDNOS), according to an adapted version of the SCID-I (see “Measurement” section) *and* a BMI of between17.5 and 40Provision of informed consentAbility to understand Dutch (speaking, listening, reading)

### Exclusion criteria

A potential participant who meets any of the following criteria will be excluded from participation in this study:Prior treatment that closely resembles CBT-E or another evidence-based intervention for eating pathology in the past 2 yearsA severe Axis-I or -II psychiatric disorder or other psychosocial circumstances that require priority of clinical attention and other support and, therefore, impedes immediate treatment of the ED (e.g., psychoses, addiction, suicidality, homelessness)Receiving ongoing psychiatric treatment (except for antidepressant medication)Intellectual disabilityMedical instability or pregnancyNot available over the coming 20 weeks

### Procedure

Each patient will be recruited at the site at which they were referred for treatment. All assessors have been trained in the adjusted SCID-I ED section which will be used to diagnose Axis-I ED. During intake potential participants receive information about the research (treatment conditions, procedure, randomization process, confidentiality) from the local assessors. The assessment staff of each site will decide whether a patient meets the inclusion or exclusion criteria and whether they are definitely eligible for the study. If this is considered to be the case, the research assistant (who is located at the logistic center of the study, PsyQ The Hague) will, for each site, randomly assign the patient to TAU or CBT-E and send an email (in attachment) to the assessor. Randomization is done by making use of a random allocation program, stratified by center and type of ED. Participation will be discussed with the patient during a second appointment with the assessor. If the patient is willing to participate and has signed the Informed Consent Form, the assessor will open the email to inform the patient of the condition they are assigned to. Data will be obtained mainly by online questionnaires, with exception of the SCID-I ED section, which will be conducted by telephone, and the IAT computer task which will be conducted on a stand-alone computer. Prior to the first treatment session, patients will be asked to fill out the online questionnaires and complete the IAT computer task. After 6, 20, 40 and 80 weeks the online questionnaires are obtained. After 20 and 80 weeks the SCID-I will be repeated. After 20 weeks the IAT task will be repeated (for an overview of the assessments see Fig. 1). Participants who do not complete the online questionnaires within 1 week will be contacted by means of personalized emails and/or telephone calls. If they decide to discontinue study participation, efforts will be made to retain them in the trial, while respecting their right to withdraw from participation at any time without further consequences. Patients will not receive any monetary compensation for their involvement, but treatment will be delivered free of charge.

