### Randomization, treatment allocation and blinding

Randomization takes place after screening of the inclusion/exclusion criteria and signing of informed consent. The research assistant will randomly assign the participating patients to CBT-E or TAU, stratified by center and type of ED (AN, BN, BED, OSFED). Within each of the twelve strata, a research assistant will randomize participants using a permuted block design. Given the nature of the psychological treatment neither the therapists nor participants can be blinded for the delivered treatment.

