### Statistical analysis

All participants who are randomized will be included in the comparison and analyzed according to their randomized allocation (intent-to-treat analysis). Wherever possible, we will continue to collect follow-up data from participants after any dropout from treatment or from the study in order to keep the dataset as complete as possible. In addition, baseline differences in study completers and dropouts will be analyzed with *t* tests for independent samples or chi-square analyses if appropriate. Moreover, we will perform a per-protocol analysis by including only those participants who completed at least 70% of the scheduled therapy sessions. All analyses will be carried out using SPSS 23 [68].

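### The article states two incompatible orders for randomisation and consent; under the Procedure section, the assessor who seeks consent already holds the unopened allocation

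*Protocol article*

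**What the plan says.** Two sections of the protocol article describe how a patient enters the trial.

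- **Procedure.** Site assessment staff decide on eligibility. If the patient is eligible, the research assistant at the coordinating centre will "randomly assign the patient to TAU or CBT-E and send an email (in attachment) to the assessor". Then: "Participation will be discussed with the patient during a second appointment with the assessor". Last: "If the patient is willing to participate and has signed the Informed Consent Form, the assessor will open the email" and tells the patient the arm.
- **Randomization, treatment allocation and blinding.** "Randomization takes place after screening of the inclusion/exclusion criteria and signing of informed consent". Allocation uses permuted blocks within twelve strata (three centres by four diagnoses).

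Three other statements bear on the point.

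- **Inclusion criteria** list provision of informed consent.
- **Statistical analysis** sets the analysis population: "All participants who are randomized will be included in the comparison".
- On the people involved, Procedure says: "All assessors have been trained in the adjusted SCID-I ED section which will be used to diagnose Axis-I ED". The blinding statement is that "neither the therapists nor participants can be blinded for the delivered treatment". It does not mention whoever conducts the SCID-I at 20 and 80 weeks, and neither does the rest of the article.

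**The concern.** The order of consent and allocation decides two things: whether the person recruiting can know the next arm, and who belongs to the randomised population. The article gives two orders, so sites cannot follow both, and a reader cannot tell which was followed.

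Under the Procedure order, the assessor holds the consent discussion with the allocation already in the inbox. If the attachment were opened early, knowledge of the arm could colour that discussion and so affect who joins each arm. Separately, anyone who declines at the second appointment has been randomised without having consented. The stated analysis population then cannot be assembled as written.

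The primary outcome is recovery judged from a SCID-I interview. The assessor who opens the email learns the arm and is trained in that interview. Whether such assessors also rate the outcome is left open.

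**Working it through.** **1. The two sequences side by side**

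| Step | Procedure | Randomization section |
|---|---|---|
| 1 | Eligibility decided | Eligibility screened |
| 2 | Arm assigned and emailed to the assessor | Consent signed |
| 3 | Second appointment: consent sought and signed | Arm assigned |
| 4 | Assessor opens the email and tells the patient | – |

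In Procedure the trigger for allocation is the eligibility decision; in the other section it is the signature. Both orders are stated outright, so condensing for a journal does not explain the difference. Because consent is an inclusion criterion, the Procedure order also allocates people who do not yet meet every criterion.

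**2. Concealment under the Procedure order.** The allocation is generated remotely by a program, which is sound. From step 2 to step 4 the recruiter holds it. The only safeguard described is the instruction on when to open the email; no password, lock or central release is mentioned.

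**3. The plan's own figure.** With recovery of 50% versus 25%, two-sided 0.05 and 80% power:

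- n = [1.96·√(2·0.375·0.625) + 0.842·√(0.5·0.5 + 0.25·0.75)]² / 0.25² = 57.7, so 58 per arm without continuity correction.
- With the correction, n′ = (n/4)·[1 + √(1 + 4/(n·0.25))]² = 65.4, so 66 per arm.

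The stated 66 per arm (132 in total) reproduces with the continuity correction. The contradiction does not alter it.

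**4. Strata.** 132/12 = 11 patients per stratum on average. By the site targets this is 60/4 = 15 at the largest centre and 36/4 = 9 at each of the other two, if diagnoses were equally common. Each decliner takes a block position that is not filled by an analysed patient.

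**5. Decliners (illustration).** The article gives no decline rate d; the values below are assumptions. Allocations needed for 132 consenting patients are 132/(1 − d). The power columns instead take 132 as the number allocated, without continuity correction (85% at d = 0). They either exclude decliners, giving 66(1 − d) per arm, or count them as not recovered, giving rates of 0.50(1 − d) and 0.25(1 − d).

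| Assumed d | Allocations for 132 consenting | Power, excluded | Power, counted as not recovered |
|---|---|---|---|
| 5% | 139 | 83% | 82% |
| 10% | 147 | 81% | 79% |
| 20% | 165 | 76% | 71% |
| 30% | 189 | 71% | 63% |

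At 10% to 30% that is 147 − 132 = 15 to 189 − 132 = 57 patients allocated but not consenting. The power loss arises only if the 132 are counted at allocation rather than at consent.

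**6. Outcome rating (illustration for the secondary point).** Assume true recovery of 37.5% in both arms, and that a share k of unrecovered CBT-E patients is scored as recovered. The false difference is 0.625·k. Exact rejection rates of the chi-square test with 66 per arm are:

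| k | False difference | Without correction | With correction |
|---|---|---|---|
| 0 | 0 | 5.2% | 3.2% |
| 5% | 3.1 points | 6.6% | 4.3% |
| 10% | 6.3 points | 11.1% | 7.8% |
| 15% | 9.4 points | 18.7% | 14.0% |

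The values of k are assumptions, and the article does not fix which version of the test will be used.

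**The case against.** The strongest defence is that the emailed attachment works like a sealed envelope. A remote research assistant prepares it, and by rule it is opened only after signature. A reader might infer that concealment is broken. The text does not support that: concealment is unsecured, and fails only if someone departs from the written rule.

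Three other stronger readings also go too far.

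- *The arm could steer the eligibility decision.* Procedure settles eligibility before allocation; only the consent discussion follows.
- *Losing decliners biases the comparison or voids the intention-to-treat analysis.* If the attachment stays unopened, neither patient nor assessor knows the arm when the patient declines. Such losses do not depend on the arm and do not bias the comparison by themselves. Lost block positions cause some imbalance, not bias. Since consent is an inclusion criterion, decliners might also be read as never having become participants. That reading is workable, but the article does not state it.
- *The primary outcome is rated by unmasked staff.* The article does not say who conducts the later interviews. Rater identity and masking may be set out in the full protocol, which is not shown. The assessor would also learn the arm if allocation followed consent, so this does not result from the early allocation.

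What stands after all this is the contradiction in order, the absence of any described safeguard beyond an instruction, and an analysis population that does not fit the Procedure order.

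**Conclusion.** The contradiction is certain; it rests on the article's wording and needs no assumption. If the Procedure order is the one in use, concealment depends on the recruiter's restraint, and patients who decline after allocation cannot be analysed as the Statistical analysis section requires. The size of that second effect is unknown: the table of decliners shows a range, not an estimate. The sample size and the other stated figures are unaffected.

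The rating point is secondary and weaker. It asks for a clarification and a simple safeguard; it does not show that ratings are unmasked. Its illustrative error rates depend on assumed misrating, and with the continuity correction the mildest scenario stays below 5%.

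**What to change.** 1. Rewrite Procedure to match the randomisation section: the research assistant runs and releases the allocation only after the assessor confirms signed consent. This changes wording and the timing of one email. The patient may learn the arm slightly later than at the appointment itself.
2. Report, by arm, any patients already allocated who declined. The trial status is still recruiting, so the change protects all remaining allocations.
3. State who conducts the SCID-I at 20 and 80 weeks, and have it done by an already-trained assessor who does not know the arm. Because the interview is by telephone, this could be someone from another of the three sites. Ask patients not to mention their treatment, and record any accidental unmasking. The cost is some cross-site scheduling, with no extra visits or staff.

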### Data management and storage

All study-related data and other study material will be stored securely at the study site (PsyQ The Hague). Participant information and study data will be kept in locked cabinets in areas with limited public access. After obtaining informed consent, participants will be allocated a unique code. The file that links participants to their codes is stored on a secure server hosted by PsyQ and is only accessible by the researcher and research assistant. Any study material concerning participant information will not be released outside the study without written permission from the participant. Online questionnaires will be collected using an authorized SurveyMonkey account and downloaded and added to the database. The SurveyMonkey security and privacy statements for Internet security and handling personal information and data can be found at, respectively, https://www.surveymonkey.com/mp/policy/security/ and https://www.surveymonkey.com/mp/policy/privacy-policy/.

Data collected on paper (SCID-I), will be manually entered into a database. Data collected by the IAT computer task will be transcripted and added to the database. Data integrity will be enforced through several ways, including valid values, range checks and consistency checks. The master database will be held on a secure server hosted by PsyQ, only accessible for authorized personnel involved in the trial. All obtained data and administrative forms (e.g., informed consent) will be stored in accordance with the data storage protocol for 15 years.

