#### Primary study parameter(s)

To test the hypothesis that CBT-E is more effective than TAU, post-treatment differences in recovery rate (based on SCID-I diagnosis) between conditions will be analyzed with chi-square analysis. Using logistic regression analysis with recovery at post treatment as outcome and treatment condition and baseline EDE-Q scores as predictors, whether differences in recovery rate between conditions are independent of severity of ED pathology at pre treatment will also be investigated. Moreover, the course of scores from pre, mid and post treatment to follow-ups I and II on the EDE-Q will be analyzed with multilevel analysis (MLA). MLA is especially suitable to analyze repeated measures data because it takes into account the dependencies among observations nested within individuals. Another advantage of this methodology is its ability to handle missing data, a problem often occurring in longitudinal research [69]. The data have a three-level hierarchical (multilevel) structure: repeated measures at the first level, individuals at the second level and treatment at the third level. Besides main effects for treatment and time, whether groups differ in their course of EDE-Q scores will be investigated by including a treatment × time interaction term. Differences between treatment centers will be investigated likewise.

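### The protocol lets the T0 questionnaires and IAT be completed after patients learn their arm, which exposes the baseline-dependent analyses but not the primary chi-square test

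*Protocol article*

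**What the plan says.** The Procedure section of the protocol article describes entry into the trial step by step. After eligibility is decided, the research assistant will "randomly assign the patient to TAU or CBT-E and send an email (in attachment) to the assessor". At a second appointment, if the patient is willing to take part and "has signed the Informed Consent Form, the assessor will open the email to inform the patient of the condition they are assigned to". The text then turns to data collection: "Prior to the first treatment session, patients will be asked to fill out the online questionnaires and complete the IAT computer task".

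Other sections bear on the order:

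- Randomization, treatment allocation and blinding: "Randomization takes place after screening of the inclusion/exclusion criteria and signing of informed consent". The T0 questionnaires are not named as a prerequisite. The same section states that "neither the therapists nor participants can be blinded for the delivered treatment".
- Data management and storage: "After obtaining informed consent, participants will be allocated a unique code".
- Primary study parameter(s): recovery on the SCID-I is compared by chi-square. A logistic regression then uses "treatment condition and baseline EDE-Q scores as predictors", and a multilevel model follows the EDE-Q from pre-treatment over all later occasions with a treatment × time term.
- Putative mediators: mid-treatment mediator scores are residualised on their pre-treatment values.
- Cost-effectiveness analysis: the EQ-5D and SF-36 are used, with the TiC-P for costs.

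**The concern.** A baseline covariate is safe to adjust for, and a baseline score is a sound starting point for change, because allocation cannot have influenced it. That guarantee is lost if the patient answers after hearing the arm. The arms are visibly different: an individual 20-session programme against usual care that may be weekly sessions or intensive group treatment. The EDE-Q, MASQ, RSE, F-MPS, IIP-32, EQ-5D and SF-36 are all self-reported. Relief, hope or disappointment at the allocation could move the answers differently in the two arms.

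Such a shift would look like chance imbalance at T0. Adjusting for it, or measuring change from it, would carry part or all of it into the estimated treatment effect. The logistic model is meant to show whether the difference in recovery is independent of initial severity, and a severity score that allocation may have moved serves that purpose poorly.

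There is also a completeness issue. A patient who leaves on hearing the arm has no T0 EDE-Q for the adjusted logistic model and no T0 mediator scores for the residuals.

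**Working it through.** **Order of events.** The two accounts, side by side:

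| Step | Procedure | Randomization, treatment allocation and blinding |
|---|---|---|
| Randomisation | after eligibility, before the consent appointment | after screening and consent |
| Disclosure to patient | directly on signature of consent | not stated |
| T0 questionnaires and IAT | before the first session | not stated |

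Participant codes are issued only after consent. Between signature and opening the email, the text describes no slot for a set of online questionnaires and a task on a stand-alone computer. Procedure also allows 1 week before patients with missing questionnaires are contacted. Neither account places T0 before disclosure. Under Procedure's order, T0 is post-randomisation in any case.

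**The plan's own figure.** Inputs from Sample size: 50% vs 25%, two-sided 0.05, power 80%.

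- Without continuity correction: n = [1.960·√(2·0.375·0.625) + 0.842·√(0.25 + 0.1875)]² / 0.25² = 57.7, so 58.
- With continuity correction: (57.7/4)·[1 + √(1 + 4/(57.7·0.25))]² = 65.4, so 66.

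The stated 66 per arm is reproduced. It rests on the chi-square comparison, which uses no T0 questionnaire, so moving T0 leaves it at 66.

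**Illustrated size of bias.** The documents give neither a shift nor a pre-post correlation. Assume a between-arm T0 shift d of 0.1 to 0.3 SD, correlation ρ = 0.5, no true effect and 66 per arm.

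- Change from T0: bias = d; SE = √(2(1−ρ))·√(2/66) = 1 × 0.174 = 0.174.
- T0 as covariate: bias = ρd; SE = √(1−ρ²)·√(2/66) = 0.866 × 0.174 = 0.151.

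| d (SD) | Change: bias | in SE | Type I error | Covariate: bias | in SE | Type I error |
|---|---|---|---|---|---|---|
| 0.1 | 0.10 | 0.57 | 8.9% | 0.05 | 0.33 | 6.3% |
| 0.2 | 0.20 | 1.15 | 21.0% | 0.10 | 0.66 | 10.2% |
| 0.3 | 0.30 | 1.72 | 40.7% | 0.15 | 1.00 | 16.9% |

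For d = 0.2 and ρ from 0.3 to 0.7, type I error runs from 16% to 32% for change and from 6.5% to 20% with T0 as covariate.

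**Adjusted logistic model.** This was simulated under no effect (1,000 runs per setting), assuming a log odds ratio of 0.5 or 0.8 per SD of EDE-Q. A T0 shift of 0.2–0.3 SD gave a spurious treatment odds ratio of 1.11 to 1.27 and rejection in 6% to 11% of runs, against about 4% with no shift. The simulated shift was towards higher T0 scores under CBT-E; a shift the other way would reverse the direction of the error.

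**The case against.** The strongest reply is that no sentence says T0 follows disclosure. Procedure sets only a latest time, the sentence opens a new topic (data collection by occasion), and the figure cited for the assessment overview is not available here. This stands. The order is the natural reading of the sequence, not an explicit rule, so the supportable statement is that the protocol permits T0 after disclosure and nowhere prevents it.

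Four stronger readings are tempting, and the documents do not support them:

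- **That the primary result is biased.** The primary test is an unadjusted chi-square on SCID-I recovery. The intake SCID-I is conducted by an assessor, not self-reported, and it and the stratification by type of eating disorder come before allocation.
- **That patients without T0 drop out of every baseline-related analysis.** In the multilevel model T0 is one of five repeated outcomes, so a patient missing only T0 can stay in. The loss concerns the adjusted logistic model and the mediator residuals. Earlier T0 collection would not stop patients leaving on hearing their arm; it would only secure their baseline.
- **That the treatment × time term carries the full shift.** That holds for a simple change from T0. In the planned five-occasion model the amount depends on how time is coded, which the article does not state.
- **That randomisation before T0 is itself the problem.** While the allocation stays concealed it cannot move the patient's answers; disclosure can.

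Finally, the 0.1–0.3 SD shift has no source in the documents, and its direction could favour either arm.

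**Conclusion.** The point holds as an avoidable risk in the secondary and adjusted analyses. Followed as written, the protocol lets self-report baselines be collected from patients who know their arm. The exposed analyses are the EDE-Q-adjusted logistic regression, the multilevel treatment × time models, the mediator residuals and, through the T0 utilities, the cost-utility analysis. The primary chi-square test and the sample size of 132 are unaffected.

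Under the assumed shift and correlation, the distortion ranges from minor (0.3 standard errors, T0 as covariate, d = 0.1) to serious (1.7 standard errors, change from T0, d = 0.3). These figures show how sensitive the analyses would be; they do not predict what will happen. Confidence is high that the protocol sets no safeguard, and only moderate that T0 is in practice completed after disclosure.

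**What to change.** For patients still to be recruited (Trial status reads as recruiting), state in Procedure that the T0 questionnaires and IAT are completed after signed consent and before the allocation email is opened, preferably before randomisation. In the same edit, reconcile Procedure with Randomization, treatment allocation and blinding on whether randomisation precedes consent.

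For patients already enrolled, record whether T0 preceded disclosure and repeat the baseline-dependent analyses as a sensitivity check without those whose T0 came later. If few patients qualify, or if timing differs by arm, that repeat is exploratory and should be labelled so.

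The cost is small: no new measures or staff and no change in sample size. The downside is that disclosure may move to later in the same appointment or be delayed by a few days.
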